### Statistics

All data will be analyzed using SPSS version 28. Baseline data and demographic characteristics will be described using descriptive statistics.

Data distribution normality will be confirmed using the Kolmogorov–Smirnov test. The main effects and interactions of group (blocked sequence, random sequence, and control), time (pre-test and post-test), and difficulty level (low, medium and high) on CoP variables will be compared using three-way repeated measures ANOVA. In addition, the main effects and interactions of groups, time (post-test and retention), and difficulty level (low, medium, and high) on CoP variables will be compared using three-way repeated measures ANOVA. Also, a one-Way ANOVA will be used to compare the means of CoP variables between the retention and transfer phases across three groups. Moreover, a two-way repeated measure ANOVA will be used to determine the main effects and interactions of group and time (pre-test, post-test, and transfer) on RT, MVT, and TRT variables of the CSRT test. A post-hoc Bonferroni test will be used for multiple comparisons.

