## Description of protocol

### Study design

This single-blind randomized controlled trial will be conducted at the Rehabilitation Research Center located at the School of Rehabilitation Sciences, Ahvaz Jundishapur University of Medical Sciences, Ahvaz, Iran.

This study consists of two sessions. The first session consists of three parts; (1) pre-intervention assessments, baseline measurements will be performed by completing the questionnaires then implementing the pre-test, (2) 15-20 minutes of 24 unexpected perturbations while standing, and (3) post-test assessments. For the patients, this session will be followed by the second session 24 hours later, which include the retention and transfer tests. An overview of the study timeline, enrollment, and time points of assessment is presented in (Table 1).

**Table 1 tbl0001:** Participant flow of enrolment, assessments and interventions.

	T0	T1	TT	T2	T3
Recruitment	+				
Interview (inclusion/exclusion)	+				
Assigning Consent form		+			
Randomization		+			
Questionnaires (MMSE; NDS; BDI-13; Mini-BEST)		+			
Assessment of reactive balance responses (balance reactions while standing in pre-test, post-test, and retention test)		+		+	+
Perturbation training intervention			+		
Transfer tests		+		+	+
Dual task test transfer (Concurrent mental arithmetic task)		+			+
Rotational mode transfer		+		+	+
Choice Stepping Reaction Time (CSRT) Test		+		+	+

T0, prior to study; T1, baseline (pre-intervention); TT, training time; T2, post-intervention test; T3, second session (one day post-intervention). Abbreviations: MMSE, Mini-Mental Scale Examination; NDS, Neuropathy Disability Score; BDI-13, Short Beck Depression Inventory; Mini-BEST, Mini Balance Evaluation Systems Test.

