### Random allocation

The stratified permuted block randomization method will be used to assign participants to one of the three groups: blocked PBBT, random PBBT, and the control group. It combines stratified randomization, which divides participants into two subgroups based on gender, with permuted block randomization, which uses blocks of treatment assignments to maintain balance within those subgroups. A random order of three letters, A (intervention with a random sequence), B (intervention with a blocked sequence), and C (control), will be made. The sequences will be put inside an opaque envelope.

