### Methods of measurement

Participants will be evaluated at a pre-test (T1), post-test (T2), and retention test (T3) using the same protocol. In these tests, each participant will receive two trials of perturbations with each of the three difficulty levels and the anterior direction with a serial sequence (totaling six trials). Serial sequence refers to the sequence or arrangement of different skills, or variations of a skill, in a specific order, one after another in a predictable manner. The post-test is applied five minutes after PBBT.

The retention test will be applied at the beginning of the second session. After a five-minute rest, patients will be tested in three different transfer tasks.

Transfer tasks will be assessed as follows:

Cognitive dual-tasking: counting backward by three from a random number selected between 100 and 200 by the outcome assessor during perturbations. Participants will be asked to maintain balance while they attempt to perform the consecutive mental subtractions task as quickly and as accurately as possible, speaking aloud the result. During this cognitive transfer task, the high level of difficulty perturbation will be applied in the anterior direction, with two trials.

Different mode of perturbation: In this test, the perturbation will be in the anterior (dorsiflexion) direction with a rotational mode, with two trials.

Choice Stepping Reaction Time (CSRT) Test: for assessing the transferability of improvements obtained in the reactive balance responses to the balance responses against internal perturbations, the CSRT test will be used. In this test, patients will stand on a long force plate of the Neurocom device with their feet hip-width apart, and while looking at the screen in front of them, colored boxes are randomly displayed on the right or left side of the screen. Participants will be instructed to step as fast as possible with the respective leg and then return to the starting position. Each participant will perform 10 trials, which include five repetitions for each direction randomly [19]. A one-minute rest period will be allowed between transfer tests. In order to have a baseline in this study, all transfer tests will be assessed before training.

Reactive balance control is the main outcome in this study, which will be recorded with the Computerized Dynamic Posturography system in the standing position [20].

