### Sample size calculation

Due to a lack of similar studies, we conducted a pilot study on 30 individuals with diabetic neuropathy (10 for each group). Sample size was calculated in G*power software version 1.9.4.3 and was based on the primary outcome of the pilot study, the difference between means of the peak CoP velocity in the anterior direction measured with the computerized dynamic posturography at T1 and T2. Based on the statistical power of 80% and the probability of the first type error of 0.05, the sample size was estimated to be about 20 individuals in each group.

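### The acquisition ANOVA uses the pre-test as an outcome level: the group main effect then estimates half the post-test difference, and the valid group-by-time test is less precise than adjusting for baseline

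*Protocol article*

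**What the plan says.** The Statistics section sets the acquisition analysis as "The main effects and interactions of group (blocked sequence, random sequence, and control), time (pre-test and post-test), and difficulty level (low, medium and high"). The method is a repeated-measures analysis of variance with these three factors, applied to the centre-of-pressure (CoP) measures. No baseline covariate is named. The section later adds "A post-hoc Bonferroni test will be used for multiple comparisons", without saying which means are compared.

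The footnote to Table 1 (Study design) gives the timing: "T1, baseline (pre-intervention); TT, training time; T2, post-intervention test". Methods of measurement confirms that the measurement is identical at each time: "Participants will be evaluated at a pre-test (T1), post-test (T2), and retention test (T3) using the same protocol". Under Random allocation, "The stratified permuted block randomization method will be used to assign participants to one of the three groups".

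The sample size of about 20 per group rests on "the difference between means of the peak CoP velocity in the anterior direction measured with the computerized dynamic posturography at T1 and T2". The stated targets are 80% power and a type I error of 0.05.

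The stepping-test (CSRT) times are analysed in the same way, by a two-way repeated-measures ANOVA in which time has the levels pre-test, post-test and transfer.

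**The concern.** Training cannot have affected a measurement made before it. When that measurement is one of two response levels, every quantity averaged over time mixes a post-test difference with a difference that is zero in expectation. The random, blocked and control question sits in the group factor, so its main effect and marginal means are natural things to read from the output, and they are diluted.

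The group-by-time term avoids the dilution because it compares changes from baseline. But a change score subtracts the whole baseline value, whereas regression on baseline subtracts only the part that predicts the post-test. The change score is therefore the noisier of the two unless the two measurements are very highly correlated. With about 20 patients per group, precision already present in the data would be left unused.

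**Working it through.** **Inputs from the article.** Three randomised groups; about 20 per group (60 in total); alpha 0.05; target power 80%; T1 before training; same test at T1 and T2.

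**Assumptions.** Equal SD s at T1 and T2, and a T1-T2 correlation r shown from 0.3 to 0.9. The article gives no effect size, SD, correlation or test family, so its figure of 20 per group cannot be reproduced. Instead, the effect is back-solved so that the change comparison has 80% power at 20 per group.

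**Step 1: what each term estimates.** Let D be the true post-test difference between two groups. The expected T1 difference is 0.

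- Group main effect: expectation (0 + D)/2 = D/2; per-patient variance s²(1+r)/2.
- Group-by-time (change): expectation D − 0 = D; per-patient variance 2s²(1−r).
- Post-test adjusted for T1: expectation D; per-patient variance s²(1−r²).

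A simulation with 20 per group, r = 0.5 and D = 1 gave mean estimates of 0.503, 0.998 and 1.000 respectively.

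**Step 2: variance of change against adjusted.** 2s²(1−r) / s²(1−r²) = 2/(1+r).

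- r = 0.3: 2/1.3 = 1.54
- r = 0.5: 2/1.5 = 1.33 (simulated 1.32)
- r = 0.7: 2/1.7 = 1.18
- r = 0.9: 2/1.9 = 1.05

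**Step 3: power, two groups of 20, two-sided 0.05, noncentral t.** 80% power for the change comparison needs a standardised difference of 0.909 on the change scale. In terms of that value, the standardised difference is 0.909 × √((1−r)/(1+r)) for the group main effect and 0.909 × √(2/(1+r)) for the adjusted comparison. The noncentrality is this value times √(20/2) = 3.162.

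| r | D/s = 0.909√(2(1−r)) | Main effect: std. diff., power | Change: power | Adjusted: std. diff., power |
|---|---|---|---|---|
| 0.3 | 1.076 | 0.667, 54% | 80% | 1.128, 93% |
| 0.5 | 0.909 | 0.525, 37% | 80% | 1.050, 90% |
| 0.7 | 0.704 | 0.382, 22% | 80% | 0.986, 86% |
| 0.9 | 0.407 | 0.209, 10% | 80% | 0.933, 82% |

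A small-sample allowance for estimating the slope lowers the adjusted figures to about 93%, 89%, 85% and 81%.

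**Step 4: three-group F test, N = 60.** The effect is again set so that group-by-time has 80% power (f = 0.411 on change). Adjusted power is 94%, 90%, 86% and 82%; main-effect power is 52%, 34%, 20% and 9%. For 80% power the adjusted analysis needs 14, 16, 18 and 20 per group, and the main effect 37, 58, 109 and 362.

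**Step 5: CSRT.** With D2 and D3 the group differences at post-test and transfer, the group main effect estimates (0 + D2 + D3)/3. This equals two thirds of the effect only if D2 = D3.

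Averaging over the three difficulty levels leaves the argument unchanged; r is then the correlation of the averaged values.

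**The case against.** The strongest reply is that group-by-time is in the plan, is unbiased for D, and matches the T1-T2 difference on which the trial was sized. That stands. A reader might infer from the dilution that the acquisition analysis is invalid, or that the trial has only about 37% power. The article does not support either reading: it never makes the group main effect its treatment test, and the low figures belong to that term alone.

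A reader might also infer that the Bonferroni comparisons are all halved. The article does not say which means they compare. Comparisons of groups at post-test, or of change, are not halved; only those on means averaged over time are. Nor is the silence on a decisive term a fault in itself, since a condensed article may leave that to the full analysis plan.

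The gain over group-by-time also depends on an r that is not given. At 0.9 it is 5% of variance and about two percentage points of power. If the effect is instead held at 0.91 SD of the post-test, power for change against adjustment is 66% and 84% at r = 0.3, 80% and 90% at 0.5, but 95% and 98% at 0.7, so the practical gain nearly disappears when r is high.

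For CSRT, equal effects at post-test and transfer cannot be presumed. The Background expects blocked practice to favour performance during training and random practice to favour retention and transfer.

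What remains is that the dilution of the main effect is exact algebra under randomisation, and that the stated model gives up precision on the term that does answer the question.

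**Conclusion.** The point holds in a limited form. The group main effect in the acquisition ANOVA, and any post-hoc comparison on means averaged over T1 and T2, estimates half the post-test difference. It is the estimate that is halved; the loss of power is not a fixed factor and grows with r. The group-by-time term is sound but has 1.54 to 1.05 times the variance of a baseline-adjusted comparison for r from 0.3 to 0.9. In power terms, that is 80% against about 93% down to 82%. For CSRT the group main effect is also diluted by including T1, by an amount that depends on the T2 and T3 effects.

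The size rests on an assumed r, equal SDs at T1 and T2, and an effect set to give the change comparison 80% power. The direction rests only on randomisation and on T1 preceding training. The change should be made, but the planned analysis is not invalid without it.

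**What to change.** Replace the acquisition ANOVA with a linear mixed model, or a repeated-measures ANCOVA:

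- response: the T2 CoP value at each difficulty level;
- covariate: the T1 value at the same level;
- fixed effects: group, difficulty and group × difficulty;
- a patient random effect, or an unstructured within-patient covariance.

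Take the Bonferroni-adjusted random-versus-blocked and training-versus-control contrasts from the group term.

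The patient term is essential, because each patient contributes three rows. In a null simulation that omitted it, the group test rejected about 16%, 22% and 29% of the time at assumed between-level correlations of 0.3, 0.5 and 0.7, against a nominal 5%.

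For CSRT, use T2 and T3 as responses, T1 as covariate, group, time and group × time as fixed effects, and a patient effect. Report the group contrasts at each time.

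If the ANOVA is kept, state at the least that group-by-time is the treatment test, and that the post-hoc comparisons are made on change or post-test values.

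The cost is analysis wording only. T1 is already collected for the CoP and CSRT measures, and the Protocol validation section says that outcome assessment had not been reached, so the change could still be specified in advance at that stage.

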Using the practice schedule concept of motor learning to PBBT is a relatively new approach [8]. There are two types of practice schedules:constant and variable. Constant practice involves repeatedly practicing a single skill. In contrast, variable practice exposes the learner to a variety of related skills [9]. Performing variable skills within a single practice session creates contextual interference (CI), a phenomenon that enhances long-term learning by requiring frequent shifts between task variations [10]. Variable practice is broadly categorized into blocked or random schedules [11]. Blocked practice, associated with low CI, involves repeated performing of one task before moving to another, facilitating skill acquisition and performance during training [11]. Random practice, associated with high CI, refers to practice task variations in the same session in a pseudo-random order [11]. Although acquisition may be slower, random practice leads to better skill retention and transfer to new situations [12].

Given the crucial role of reactive responses in preventing falls, which are often sudden and occur in any direction [13], it is important to investigate how different practice schedules affect the ability of individuals with DPN to react to balance perturbations. In addition, In individuals with DPN, compensating for sensory loss increases cognitive demand, causing balance impairments during dual-tasking [6]. Since reactive balance requires attention, dual tasks may further disrupt postural control strategies in these individuals [14]. Therefore, assessing the generalizability of improvements in reactive balance control during single-task to dual-tasks may be useful for enhancing dual-task interference on reactive balance performance in individuals with DPN.

To the best of our knowledge, no study has yet investigated the effects of different practice schedules of PBBT on reactive balance control in individuals with DPN. Therefore, this study aims to compare the effects of blocked and random practice of PBBT on the acquisition, retention, and generalizability of acquired reactive balance skills in individuals with DPN. Our findings would be helpful for the development of preventive and therapeutic strategies to reduce the risk of falls and improve reactive balance control in individuals with DPN.

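### The stated retention ANOVA for the CoP variables tests loss since the post-test, and no stated CoP analysis clearly tests the baseline-adjusted group difference at 24 hours

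*Protocol article*

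**What the plan says.** The Background of the protocol article sets the aim: to "compare the effects of blocked and random practice of PBBT on the acquisition, retention, and generalizability of acquired reactive balance skills". Retention is thus one of three named targets.

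The Statistics section splits the CoP analysis into two models, each with two time levels. The first takes group, "time (pre-test and post-test), and difficulty level (low, medium and high) on CoP variables will be compared using three-way repeated measures ANOVA". The second, which bears on retention, takes "the main effects and interactions of groups, time (post-test and retention), and difficulty level (low, medium, and high) on CoP variables". Neither sentence mentions a baseline covariate. One other CoP analysis uses the retention data: "a one-Way ANOVA will be used to compare the means of CoP variables between the retention and transfer phases across three groups".

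The baseline needed for a comparison with T1 is collected. Under Methods of measurement, "Participants will be evaluated at a pre-test (T1), post-test (T2), and retention test (T3) using the same protocol". For the stepping test the same Statistics section does put the pre-test in the model: "group and time (pre-test, post-test, and transfer) on RT, MVT, and TRT variables of the CSRT test".

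The Background also states what pattern to expect. Blocked practice is described as "facilitating skill acquisition and performance during training", while for random practice, "Although acquisition may be slower, random practice leads to better skill retention and transfer to new situations".

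**The concern.** With time limited to T2 and T3, the interaction asks whether groups lost different amounts overnight. The retention question in the aim is also about how much benefit each group still holds at 24 hours, and those two quantities can differ. An arm with a larger gain at T2 that partly fades shows decay. An arm with a smaller gain that stays put shows none. An untrained control with no gain has nothing to lose and also shows none. The Background makes a higher T2 under blocked practice plausible, so this is not a remote case.

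The group main effect of the same model does not fill the gap, because it mixes the T2 difference into the T3 difference. At stake is the label put on the random-versus-blocked result: better retention could be claimed when 24-hour benefit is equal, or a durable advantage could be missed by someone looking only at the interaction.

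**Working it through.** **Inputs.** The protocol gives about 20 per group (Sample size calculation). That figure comes from peak anterior CoP velocity at T1 and T2, with 80% power and a type I error of 0.05. No effect size or SD is stated, so it cannot be reproduced; it serves here only as n. The effects, the unit SD and the correlation r are assumptions, shown over a range. Gains are coded so that higher is better, with one value per participant and time point (averaged over difficulty).

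**What each term estimates, random (R) versus blocked (B).**
- Group-by-time interaction: (R3 − R2) − (B3 − B2). T1 does not enter.
- Group main effect: (R2 + R3)/2 − (B2 + B3)/2.
- Benefit held at 24 hours: (R3 − R1) − (B3 − B1), or R3 − B3 adjusted for T1.

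**Case 1, equal benefit at 24 hours.** Over T1, T2, T3, let blocked be 0, 1.0, 0.5 SD and random 0, 0.5, 0.5 SD.
- Interaction: (0.5 − 0.5) − (0.5 − 1.0) = 0.5 SD in favour of random.
- Main effect: 0.5 − 0.75 = −0.25 SD, in favour of blocked.
- Benefit at T3: 0.5 − 0.5 = 0.

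The two model terms point in opposite directions, and neither returns the zero difference at T3.

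Power of the interaction contrast: SD of T3 − T2 = √(2(1 − r)); noncentrality = (0.5/SD) × √(20/2); two-sided t with 38 df. The Bonferroni column assumes three pairwise comparisons, 0.05/3 = 0.0167.

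| r | SD of change | Noncentrality | Significant at 0.05 | At 0.0167 |
|---|---|---|---|---|
| 0.5 | 1.000 | 1.58 | 34% | 19% |
| 0.6 | 0.894 | 1.77 | 41% | 24% |
| 0.7 | 0.775 | 2.04 | 51% | 33% |
| 0.8 | 0.632 | 2.50 | 68% | 50% |

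A simulation (10,000 runs, 20 per group, equal correlations, alpha 0.05) agrees: 34%, 50% and 68% at r = 0.5, 0.7 and 0.8. With the T2 excess for blocked varied over 0.3, 0.5 and 0.8 SD, the interaction contrast is significant in 15% to 98% of runs and the blocked-versus-random main effect in 7% to 30%. The same contrast on T3 − T1 is significant in 4.5% to 5.2%, and a comparison at T3 alone in about 5%.

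**Case 2, random durably better, no forgetting.** Let blocked be 0.5 SD at T2 and T3, and random 1.3 SD at both. The interaction is 0 − 0 = 0, so it rejects in about 5% of runs. The main effect is 1.3 − 0.5 = 0.8 SD and detects the difference in 74% to 82%. T3 − T1 detects it in 69%, 89% and 98% at r = 0.5, 0.7 and 0.8.

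**Case 3, both trained groups hold 0.8 SD over control, no forgetting.** The three-group interaction again rejects in about 5%; the three-group main effect rejects in 77% to 84%.

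**What baseline adjustment adds at T3.** The variance of the outcome is 1 for T3 alone, 2(1 − r) for T3 − T1, and 1 − r² for T3 adjusted for T1. At r = 0.5, 0.7 and 0.8 the last two are 1.00, 0.60, 0.40 and 0.75, 0.51, 0.36. Adjustment gives the smallest variance at each of these correlations.

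**The case against.** The case for leaving the plan alone is substantial, and much of it stands.

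- T2-to-T3 change is a legitimate quantity. The Abstract asks about persistency, and whether a gain lasts overnight is exactly that change. Read beside the T1-T2 model, the decay in case 1 would be visible.
- The model lists all main effects and interactions, with Bonferroni post-hoc tests. Nothing says the interaction decides retention, and cases 2 and 3 show that the group main effect has power for durable differences.
- The one-way ANOVA could be read as comparing the three groups at retention, and a post-hoc test could do the same. Under randomization a T3-only comparison is valid without baseline and loses only precision. However, the wording equally admits retention versus transfer, so it cannot be counted on to supply the contrast.
- The effects and correlations are assumed; the protocol gives none.

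Two stronger readings are tempting and should be set aside. A reader might infer that an arm gaining more at T2 can only look worse. That is false: if it keeps the whole gain its T2-T3 change is zero, and if it improves further it looks better. A reader might also take 34% to 68% as a false-positive rate. It is power to detect a decay difference that is real in case 1; the error would lie in calling that difference better retention.

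What survives is narrower. The time levels are written out, they exclude T1, and no stated CoP analysis clearly gives the group difference at T3 adjusted for baseline.

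**Conclusion.** The point holds in this limited form. That the interaction measures T3 − T2, and that the main effect blends T2 with T3, follows from the stated time levels and needs no assumption. The consequences depend on how the result is read and on the assumed values: in case 1 a random-versus-blocked contrast significant in 34% to 68% of trials (19% to 50% at 0.0167) despite equal 24-hour benefit, and in case 2 an interaction that rejects only about 5% of the time despite a 0.8 SD durable advantage.

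A reader might conclude that the whole retention analysis is invalid or tilted toward one arm. The documents do not support that, since no term is named as decisive and other terms or post-hoc tests can be informative. Severity is moderate: retention is a named aim, but the T1-T2 comparison on which the trial is sized is unaffected and the data for a better contrast are collected anyway.

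**What to change.** State retention as the between-group difference at T3 adjusted for T1. One model is enough: T2 and T3 as responses, T1 as covariate, and group, time and difficulty with their interactions. Name the random-versus-blocked and training-versus-control contrasts at T3 in advance, and say which multiplicity adjustment applies to them. Report the T2-to-T3 change separately, labelled as decay or persistence. State also whether the one-way ANOVA compares groups or compares retention with transfer.

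This costs analysis wording only: no extra visits, measurements or participants. Under Protocol validation the article says the outcome assessment phase has not been reached, so the change can be made before results are seen.

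### The CoP comparison of retention with transfer is paired, but the named one-way ANOVA has no within-patient term and, as written, does not test whether carry-over differs by group

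*Protocol article*

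**What the plan says.** Methods of measurement places both sets of measurements in session 2: "The retention test will be applied at the beginning of the second session", and then "After a five-minute rest, patients will be tested in three different transfer tasks". Every patient therefore has a retention value and transfer values from the same visit.

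For the CoP variables, Statistics states: "Also, a one-Way ANOVA will be used to compare the means of CoP variables between the retention and transfer phases across three groups". It names no difference score, no patient term and no interaction for this comparison.

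The neighbouring analyses are specified differently. The analysis of post-test against retention covers "the main effects and interactions of groups, time (post-test and retention), and difficulty level (low, medium, and high) on CoP variables" by three-way repeated measures ANOVA, and the analysis of pre-test against post-test has the same form. For the Choice Stepping Reaction Time (CSRT) test, "a two-way repeated measure ANOVA will be used to determine the main effects and interactions of group and time (pre-test, post-test, and transfer" phases).

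The aim given in Background is to "compare the effects of blocked and random practice of PBBT on the acquisition, retention, and generalizability of acquired reactive balance skills".

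**The concern.** The sentence involves two factors: phase, which varies within a patient, and group, which varies between patients. A one-way ANOVA has one factor, treats all observations as independent and has no interaction. It is the only comparison of phases or time points in the section that is not named as a repeated measures analysis.

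Two things are at stake for the dual-task and rotational tests. First, the error term may be wrong, in a direction that depends on how the sentence is carried out. Second, whether performance carries over differently after random, blocked or no practice is the group by phase term, and the named test does not contain it. For CoP, this sentence is the only analysis given for the generalizability part of the aim.

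**Working it through.** **Inputs.** There are about 20 patients per group and 60 in total (Sample size calculation; Inclusion and exclusion criteria). Retention and transfer are paired (Methods of measurement). The protocol gives no within-patient correlation r between retention and transfer CoP, so r = 0.3, 0.5 and 0.7 are assumptions. Both phases are given the same SD, and the nominal two-sided level is 5%. The plan states no figure for this analysis, so there is none to reproduce. The sample size rests on T1 and T2 and is not affected.

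**1. Phase as the factor (plain reading).** In SD units, for 20 patients:

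- SE assumed under independence: √(2/20) = 0.316.
- Correct paired SE: √(2(1 − r)/20).

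| r | Paired SE | SE too large by 1/√(1 − r) | True type I error | Power where a paired test has 80% |
|---|---|---|---|---|
| 0.3 | 0.265 | 1.20 | about 2% | about 70% |
| 0.5 | 0.224 | 1.41 | about 0.7% | about 54% |
| 0.7 | 0.173 | 1.83 | about 0.1% | about 27% |

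The last two columns come from simulation of bivariate normal pairs. The power column uses a standardised paired difference of 0.66, which gives a paired t-test 80% power at n = 20. Pooling the three groups (60 against 60) gives much the same type I error: 2.0%, 0.6% and 0.1%.

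**2. Group as the factor, both phases stacked.** Each group then contributes 40 values from 20 patients. The variance of a group mean is (1 + r)/40, but the test assumes 1/40. The true variance is therefore 1.3, 1.5 or 1.7 times the assumed one, and simulated type I error is about 10%, 14% and 17%.

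These are upper figures, because they assume equal phase means. A phase shift of δ SD adds about δ²/4 to the error variance. With δ = 1 the ratio becomes (1 + r)/1.25 = 1.04, 1.20 and 1.36, and type I error drops to about 6%, 8% and 11%.

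**3. All six group-by-phase cells in one one-way ANOVA.** A group contrast built from the cells has type I error of about 10%, 13% and 17%. An interaction contrast has 1.5%, 0.3% and below 0.1%, so real differences in carry-over would tend to be missed.

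**4. Separate one-way ANOVAs of the three groups within each phase.** Each patient contributes one value to each test, and type I error is about 5% at every r. Carry-over by group is still not tested.

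**5. One-way ANOVA on each patient's transfer-minus-retention difference.** Type I error is about 5% at every r. With two phases this is the group by phase test, on 2 and 60 − 3 = 57 degrees of freedom.

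**The case against.** The strongest reply is that the sentence is loosely worded and has sound meanings. Separate comparisons of the groups at retention and at transfer (reading 4) have correct standard errors, and a group comparison at the transfer test bears on the aim. A one-way ANOVA of difference scores (reading 5) would be fully adequate. This stands in part. A reader might infer that the standard errors are wrong whatever was meant, and the documents do not support that. But the sentence says that the phases are what is compared, which does not fit reading 4, and no difference score is named, which leaves reading 5 without textual support.

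A reader might also infer that the whole transfer aim is invalid. It is not. The CSRT transfer analysis is a repeated measures ANOVA with group, time and their interaction, and the acquisition and retention analyses are likewise repeated measures.

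Nor can it be said that the plan generally risks false positives. On the plain reading the error is conservative and the loss is power. Inflation needs the phases to be stacked, which the text does not state, and it shrinks if the phase means differ. That is plausible when transfer adds a cognitive load or a rotational mode. Finally, the question can be answered with the data being collected; it is the named test that does not answer it.

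**Conclusion.** The sentence is wrong as written: it applies a one-factor test for independent observations to paired data with two factors. That carry-over by group goes untested holds on every reading except the unnamed difference score (and reading 3, where it could be reached only through a contrast with the wrong error term). The effect on standard errors depends on the reading. Type I error at a nominal 5% runs from about 0.1% (phase as the factor, r = 0.7) to about 17% (stacked, r = 0.7, equal phase means), and is about 5% for separate tests within each phase. On the plain reading, power falls from 80% to between about 70% and 27%. All these figures rest on the assumed correlations, equal SDs and 20 patients per group. The point is limited to CoP in the dual-task and rotational transfer tests.

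**What to change.** Replace the sentence with a two-way mixed (repeated measures) ANOVA, or a mixed model with a patient effect, containing group, phase (within patient) and group by phase. Run it once for dual-task and once for rotational transfer. State that the group by phase term is the test of differential carry-over, with the Bonferroni comparisons already planned to follow it.

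Name the retention comparator for each run. Retention consists of "two trials of perturbations with each of the three difficulty levels and the anterior direction with a serial sequence (totaling six trials"), while the dual-task test uses two high-difficulty anterior trials only. Its comparator should be the high-difficulty retention trials, because averaging over all levels would mix phase with difficulty. The rotational test has no such direct match in what the article states, so its comparator needs to be fixed in advance.

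The cost is analysis wording only, with the same data and the same software. Protocol validation says that the outcome assessment phase has not been reached, so the change can be recorded before results are seen.
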